**Secondary aims:**

1. To determine, using sensitive magnetic methods, the effect of each ACT regimen on gametocyte carriage during the six-week trial follow-up period.

2. To determine the duration of post-treatment prophylaxis using passive case detection of symptomatic malaria infections presenting over a period of six months after trial follow-up.

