**RESEARCH PLAN**

We will perform the clinical studies at i) Alexishafen and Mugil Clinics, Madang Province, sites we have used for various studies since 2001 and which have proven recruitment potential and excellent facilities,CIA#31 and ii) Vunapope Hospital, East New Britain Province which also has a busy clinical load and laboratories which have been used by the PNG Institute of Medical Research (IMR) for malaria studies. Maprik in the East Sepik may be brought in as an additional site depending on recruitment. Laboratory studies (host/parasite genotyping, drug assays and/or biochemical testing) will be conducted at Vunapope; the IMR laboratories at Yagaum Hospital, Madang Province; the University of Western Australia (UWA) School of Medicine and Pharmacology and the Biochemistry Department at Fremantle Hospital; the Pharmacy School, Curtin University. Relevant techniques are well established in these institutions.

**Main Study: A trial of the tolerability, safety, efficacy and cost-effectiveness of AL, AP and AN in PNG children with uncomplicated falciparum or vivax malaria** *(Primary aim)*

*Background:* Since pyronaridine11-14 and naphthoquine16 are active against CQ-resistant falciparum malaria and have a t½*e* that is at least that of lumefantrine (4-6 days), AP and AN should have similar efficacy over 42 days of follow-up to AL in this situation. We postulated that the greater efficacy of DP vs AL against *P. vivax* reflects, in part, the longer piperaquine t½*e* (3-4 weeks), in which case the efficacy of AP and perhaps AN should equate with that of DP. However, the similar low efficacy of AL and CQ-SP in areas with known CQ-resistant *P. vivax* means that other factors may underlie the poor response to AL in our recent trial.8

*Operational principles:* We will conduct the study using standard operating procedures, under Good Clinical Practice guidelines, in accordance with the Helsinki Declaration, and with ethical approval from the PNG Ministry of Health Medical Research Advisory Committee and the UWA Human Research Ethics Committee. Although the trial is open-label, there will be an independent Data and Safety Monitoring Committee (DSMC) and external monitoring of sites.

*Endpoints:* The primary endpoint will be:

1. recrudescent *P. falciparum* within 42 days after correction for re-infections using PCR genotyping of polymorphic parasite loci19, 20 in children with falciparum malaria, or

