*Background:* We have developed HFGMF gametocyte detection based on the unique metabolism of iron in the parasite and commercially available magnetic separation columns (Miltenyi Biotech). The method relies on magnetic concentration of gametocytes which are then identified more readily on a smear (see Figure 2) than by conventional expert microscopy.29 It has a similar sensitivity to reverse transcriptase PCR (RTPCR, data submitted; see Table), but is much quicker and cheaper.

[figure not shown]

| Gametocyte density | HFGMF (time taken) | Thick film (time taken) | RT-PCR |
| --- | --- | --- | --- |
| 2,970/µL | Positive (<1 minute) | Positive (<1 minute) | Positive |
| 297/µL | Positive (<1 minute) | Positive (7 minutes) | Positive |
| 29.7/µL | Positive (<1 minute) | Positive (28 minutes) | Positive |
| 2.97/µL | Positive (9 minutes) | Negative | Positive |
| 0.297/µL | Negative | Negative | Negative  HFGMF detection at 3/μL |

The method could be used to quantify the gametocidal efficacy of ACT assuming that transmission is unlikely at a gametocyte density <3/μL,30 a threshold detectable by HFGMF but not microscopy.

*Methods:* We will take a small additional sample of mixed capillary blood at each follow-up visit from 25 children in each treatment and species arm on which HFGMF and RTPCR will be performed as well as conventional microscopy. The differences in gametocyte carriage by detection method over time between treatment arms will be determined using General Linear Modelling for repeated measures, applying square-root transformation to allow for the effect of zero values on the density distribution at each time point and identifying important non-treatment-related covariates.

**Sub-study 2: Duration of post-treatment prophylaxis using passive case detection of symptomatic malaria during the six months after trial follow-up** *(Secondary Aim 5)*

*Hypothesis:* The duration of post-treatment prophylaxis for AL, AP and AN is a function of the t½*e* of the non-artemisinin partner drug alone.

*Background:* For some long half-life drugs such as piperaquine, urinary excretion studies suggest unexpected persistence of low plasma concentrations.31 In addition, the antimalarial activity of atovaquone in sera is sustained beyond that predicted by its pharmacokinetic properties.32 Whether these sorts of effects are of clinical importance in ACT-treated patients is unknown, even for DP.

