*Methods:* We will carry out a 6-month period of passive case detection of all trial patients with an ACPR after trial close-out through surveillance of clinic/inpatient records for confirmed malarial episodes at i) Alexishafen/Modilon Hospital and ii) Rabaul Hospital/neighbouring clinics. Our established presence at both sites and our relationship with local health care staff should enable us to overcome potential problems with ascertainment using existing information systems. To examine the effect of treatment on long-term outcome, we will perform a Cox regression analysis of time to first appearance of i) any parasitaemia in-trial or post-trial, and ii) because LPF would not be ascertained during post-trial follow-up, any symptomatic parasitaemia in-trial or post-trial. The mean time to event in each treatment group will be compared with the t½*e* for each scenario.

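### Sub-study 2 compares time to any parasitaemia with partner-drug half-life, so P. falciparum recrudescence counts as loss of prophylaxis and cure-rate differences enter a comparison about duration of protection

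*Protocol*

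**What the plan says.** The second secondary aim of the protocol is "To determine the duration of post-treatment prophylaxis using passive case detection of symptomatic malaria infections presenting over a period of six months" after trial follow-up. The Sub-study 2 hypothesis reads "The duration of post-treatment prophylaxis for AL, AP and AN is a function of the" elimination half-life of the non-artemisinin partner drug, and of that alone.

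The Sub-study 2 Methods introduce the analysis as an examination of treatment's effect on long-term outcome, and state "we will perform a Cox regression analysis of time to first appearance of i) any parasitaemia in-trial or post-trial". A second event is added: "because LPF would not be ascertained during post-trial follow-up, any symptomatic parasitaemia in-trial or post-trial". Then: "The mean time to event in each treatment group will be compared with" the elimination half-life. Children with an ACPR are followed by passive case detection for six months after the trial.

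In the Main Study, the primary endpoint for falciparum malaria is recrudescence within 42 days "after correction for re-infections using PCR genotyping of polymorphic parasite loci". PCR-uncorrected reappearance is a separate secondary endpoint. Parasitaemia arising on Days 4 to 42 is classed as late parasitological failure (LPF) or, with fever, late clinical failure.

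**The concern.** Prophylaxis after treatment means protection against a new infection, or suppression of a vivax relapse, once the treated infection has cleared. A recrudescence shows that the treated infection was not cleared. It carries no direct information on when protection against new infection ended.

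Under both event definitions, a child with a PCR-confirmed recrudescence on Day 21 and a child with a new P. falciparum genotype on Day 21 get the same event and the same time. The symptomatic version does this for febrile recrudescences. The main study plans the genotyping that tells these children apart, but the sub-study does not use it.

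At stake is the reading of the half-life hypothesis. Two partner drugs with identical protection against new infection would show different mean event times whenever their recrudescence rates differ. The hypothesis could then be rejected or supported for a reason unrelated to prophylaxis.

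**Working it through.** The protocol gives no sample size, event count or power for Sub-study 2, so there is no stated figure to reproduce. The check has two parts.

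**1. Does recrudescence count as an event?**

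- The first event is any parasitaemia, in-trial or post-trial, with no restriction by genotype or type of failure.
- The symptomatic event is added because LPF cannot be ascertained after the trial. In-trial LPF therefore counts in the first event, and LPF as defined covers every parasitaemia on Days 4 to 42, recrudescent or new.
- The ACPR phrase is attached to the post-trial case detection. The Cox sentence separately names in-trial events.

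As written, recrudescence counts.

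**2. How large is the effect?**

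Inputs from the protocol:

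- Day 42 PCR-corrected failure on AL in the previous trial: 100 − 95.2 = 4.8% (Background).
- At the 5-point non-inferiority margin: 4.8 + 5 = 9.8% (Sample sizes).
- On DP in the previous trial: 100 − 88.0 = 12% (Background).

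Assumptions, not in the protocol:

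- These failures are all recrudescences, spread evenly over Days 7 to 42.
- The new-infection hazard is constant and equal in both arms, so the true hazard ratio (HR) is 1. The 42-day risk p is 10%, 20% or 40%.
- Recrudescence and new infection are independent.
- Six months after Day 42 is 42 + 182 = Day 224.

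To Day 42, the ratio of cumulative hazards with recrudescence rates r₁ and r₀ is

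HR ≈ [−ln(1−p) − ln(1−r₁)] / [−ln(1−p) − ln(1−r₀)].

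The recrudescence terms are 0.049 (4.8%), 0.103 (9.8%) and 0.128 (12%). The new-infection terms are 0.105, 0.223 and 0.511. For example, at p = 20% and 9.8%: (0.223 + 0.103) / (0.223 + 0.049) = 1.20.

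To Day 224, event-free survival in each arm is S(t) = exp(−λt) × [1 − r·G(t)]. Here λ = −ln(1−p)/42, and G(t) = (t−7)/35, held between 0 and 1. The HR is the large-sample solution of the Cox score equation for these two curves.

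| p by Day 42 | To Day 42, 9.8% v 4.8% | To Day 42, 12% v 4.8% | To Day 224, 9.8% v 4.8% | To Day 224, 12% v 4.8% |
| --- | --- | --- | --- | --- |
| 10% | 1.35 | 1.51 | 1.11 | 1.16 |
| 20% | 1.20 | 1.29 | 1.07 | 1.10 |
| 40% | 1.10 | 1.14 | 1.04 | 1.06 |

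Mean event-free time to Day 224 (the area under S) falls from 164.3 to 156.9 days at p = 10%, and from 74.1 to 71.3 days at p = 40%, for 4.8% v 9.8%.

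Simulation under the same assumptions (60,000 children per arm) gave 1.09 to 1.52 at Day 42 and 1.04 to 1.17 at Day 224. A second, smaller simulation (4,000 per arm) assumed full protection to Day 20, recrudescence over Days 14 to 42, and follow-up to Day 222. It gave 1.04 to 1.14 over the full horizon.

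**Scale against precision.** If the 515 falciparum children are spread over three arms, there are about 172 per arm. Even if every child has an event, SE(log HR) ≥ √(1/172 + 1/172) = 0.108. The spurious log HR, from ln 1.04 = 0.039 to ln 1.17 = 0.157, is then 0.4 to 1.5 standard errors at most, and less with fewer events.

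**The case against.** **The stated purpose is long-term outcome.** For that purpose, first parasitaemia of any origin is a reasonable event, and this stands. It does not cover the next step, where the same event time is compared with the half-life under a hypothesis about prophylaxis.

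**The ACPR restriction may already remove recrudescences.** The protocol says that the primary endpoints constitute ACPR, and for P. falciparum that endpoint is PCR-corrected. If the whole sub-study cohort were limited to such children, in-trial events would be re-infections or P. vivax. The LPF clause alone does not rule this out, since re-infections are LPF too. But the restriction is attached to post-trial case detection, and the Cox sentence does not repeat it. If a restricted cohort is intended, the text needs to say so.

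**The bias is small in this setting.** The protocol describes intense transmission of several species and expects similar efficacy between arms, which points to the low end of the range. The 12% figure belongs to DP, an arm only if AN is withdrawn. This stands and limits the weight of the point.

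**Censoring is not clean.** Low drug exposure could drive both recrudescence and early re-infection, which would make the censoring informative. This also stands. It is a reason to show both analyses.

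**Other endpoints reveal cure-rate differences.** Corrected and uncorrected P. falciparum and any P. vivax are reported separately to Day 42. A careful reader could see that cure rates differ, but could not remove their effect from the half-life comparison.

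**Conclusion.** The point holds for PCR-confirmed P. falciparum recrudescence up to Day 42. The half-life comparison mixes cure with duration of protection, and an arm with a lower cure rate will look shorter-acting. Over the horizon that the sub-study uses, the spurious HR is roughly 1.04 to 1.17 under the assumptions shown. It approaches 1 when cure rates are close or new infection is frequent.

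Three stronger readings might be inferred, and the documents do not support them:

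- **That early treatment failures certainly count as events.** The event is a first appearance, and parasites that never cleared by Day 3 do not clearly appear. The text does not name early failure here. It is a gap to close, not an established error.
- **That the size of the bias is the Day 42 figure, about 1.09 to 1.52.** The analysis runs six months further, and the later events dilute it.
- **That censoring restores an HR of 1.** It does so in these calculations only because recrudescence and new infection were assumed independent.

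This concerns a secondary aim and leaves the primary endpoint untouched. It merits correction because the remedy is specific and cheap.

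**What to change.** In the Sub-study 2 Methods:

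- For children treated for P. falciparum, base the half-life comparison on time to first new infection: in-trial P. falciparum typed as re-infection, any in-trial P. vivax, or any post-trial episode. Censor at PCR-confirmed recrudescence (cause-specific Cox model), and calculate the mean event times under the same rule.
- Apply the same rule to the symptomatic version.
- State that the ACPR restriction governs post-trial surveillance only, and state how the analysis handles children who have not cleared parasites by Day 3.
- Keep time to any parasitaemia as the long-term outcome, without comparing it with half-life, and report the two analyses side by side.

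The cost is analysis wording. P. falciparum genotyping to Day 42 is already planned for the primary endpoint, and no visit, sample or child is added. The downsides are slightly fewer events and possibly informative censoring. Post-trial P. falciparum is untyped and would be taken as new. Vivax relapse cannot be separated from re-infection, so nothing changes for children treated for P. vivax. These limits should be stated with the result.

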2. AP (Pyramax) as artesunate 3 mg/kg and pyronaridine tetraphosphate 9 mg/kg once-daily for three days, and
3. AN (Arco) as artemisinin 20 mg/kg and naphthoquine phosphate 8 mg/kg once-daily for three days (as justified above).

Combinations of full, half- or quarter-tablets will be swallowed whole or crushed lightly before administration. AL-treated subjects will be given tablets or suspension with milk; because there is no such recommendation for AP or AN, pharmacokinetic studies our group will perform during 2009 will determine whether these ACTs should also be given with milk. Only the evening AL doses will be unsupervised, being given at home by parents/guardians. Children vomiting within 30 minutes will be re-treated.

Standardized review including microscopy will be scheduled on Days 1, 2, 3, 7, 14, 28 and 42, with all data, including symptoms, unscheduled clinic visits and non-study treatment, entered on detailed case report forms. Children developing uncomplicated or severe malaria will be given DP at the clinic or intramuscular artemether at the local referral hospital, respectively as per the most recent PNG National Treatment Guidelines.23 All blood films will be re-examined by two skilled microscopists blinded to treatment. Slides discrepant for positivity/negativity, speciation or parasitaemia (>3x difference) will be adjudicated by a senior microscopist. The primary endpoints constitute ACPR under WHO-recommended assessment.24 Early treatment failure (ETF) will be taken as the development of severity or an inadequate parasitological response by Day 3. Any child developing parasitaemia between Days 4 and 42 will be considered late parasitological failure (LPF) or, if febrile, late clinical failure (LCF).

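### Sub-study 2, analysis (i): the event changes from any parasitaemia to recorded symptomatic malaria after Day 42, yet its mean time to event is still compared with half-life

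*Protocol*

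**What the plan says.** In the Main Study (Clinical/laboratory procedures), detection is active: "Standardized review including microscopy will be scheduled on Days 1, 2, 3, 7, 14, 28 and 42". Parasitaemia from Day 4 to Day 42 is late parasitological failure (LPF), or late clinical failure if the child is febrile.

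In Sub-study 2 (Methods), detection becomes passive: "We will carry out a 6-month period of passive case detection of all trial patients with an ACPR after trial close-out". Events in this period are to be found "through surveillance of clinic/inpatient records for confirmed malarial episodes". No post-trial blood films are scheduled.

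The same paragraph names two Cox analyses. The first is of "time to first appearance of i) any parasitaemia in-trial or post-trial". The second is, "because LPF would not be ascertained during post-trial follow-up, any symptomatic parasitaemia in-trial or post-trial". No censoring at Day 42 is stated for the first.

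On use of the results, the protocol says: "The mean time to event in each treatment group will be compared with the" half-life, and this applies to each scenario, so to (i) as well as (ii). The Sub-study 2 hypothesis is that duration of prophylaxis depends on that half-life alone.

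**The concern.** Until Day 42 an event in (i) is any positive slide. After Day 42 it is an illness that led to a visit and a confirmed record. Time at risk runs on across that change. Analysis (i) therefore estimates neither time to any parasitaemia nor time to symptomatic malaria. A child who becomes parasitaemic without symptoms on Day 60 stays in the risk set as event-free until a later confirmed illness, or to the end of follow-up if there is none.

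This matters because the time from (i) is one of the quantities set against half-life, the test that Sub-study 2 exists to make. Missed post-trial infections lengthen the apparent event-free time for reasons unrelated to the drug.

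**Working it through.** The protocol gives no rate, power or hazard ratio (HR) for Sub-study 2, so there is no stated figure to reproduce.

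**Inputs.** From the protocol: scheduled slides to Day 42, then six months passive. Taking six months as 182 days, maximum follow-up is 42 + 182 = 224 days, of which 182/224 = 81% has no detection of symptom-free parasitaemia. That is a maximum, reached only by children with no event. Assumed: 42-day risk on artemether-lumefantrine (AL) of 20%; constant hazard; symptom-free share q of 30%, 50% or 70%; mean time to event read as mean event-free time within 224 days.

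**Hazard.** λ = −ln(0.80)/42 = 0.00531 per day. After Day 42 the detected hazard is λ(1 − q), so the post-trial rate is too low by exactly q.

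**Mean event-free time.** M(q) = 0.20/λ + 0.80 × [1 − exp(−λ(1 − q) × 182)] / [λ(1 − q)]

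- q = 0: 37.6 + 93.3 = 131.0 days
- q = 0.3: 37.6 + 0.80 × 0.4918/0.003719 = 143.4 days
- q = 0.5: 37.6 + 0.80 × 0.3834/0.002657 = 153.1 days
- q = 0.7: 37.6 + 0.80 × 0.2518/0.001594 = 164.0 days

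**Rate over the whole 224 days** = detected proportion / M(q) × 365.25. At q = 0 this is 0.696/131.0 × 365.25 = 1.94 per child-year. At q = 0.3, 0.5 and 0.7 it is 1.51, 1.21 and 0.89, or 22% to 54% too low.

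**Same formula at the protocol's vivax figure** (Sample sizes: Day 42 ACPR 30.3% on AL, so risk 69.7%). λ = −ln(0.303)/42 = 0.0284. Mean event-free time goes from 35.1 to 39.3, 44.2 and 52.5 days. The direction is the same.

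**Reading of the mean.** If mean time were instead a plain average over children with a detected event, it would be wrong in the other direction, because the missed events are late ones. At 20% risk it is 90.3 days at q = 0. At q = 0.5 it is (0.20 × 20.2 + 0.307 × 125.7)/0.507 = 84 days.

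**Hazard ratio.** Large-sample Cox estimate θ, two equal arms, true HR 0.5 to Day 42, from Σ[h₁S₁(1 − p) − h₀S₀p] = 0 with p = θS₁/(S₀ + θS₁), where h is the detected hazard and S the proportion still counted at risk:

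| Situation (42-day risk 20%) | q = 0 | 0.3 | 0.5 | 0.7 |
|---|---|---|---|---|
| HR stays 0.5; missed infections leave later risk unchanged | 0.50 | 0.50 | 0.50 | 0.50 |
| HR becomes 1 after Day 42; later risk unchanged | 0.86 | 0.83-0.84 | 0.81 | 0.76 |
| HR stays 0.5; missed infections never seen again | 0.50 | 0.53 | 0.54 | 0.54 |

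Detection is equal in both arms in every row. At the vivax risk of about 70%, the waning case moves only from 0.67 to 0.65-0.67. If the effect wanes and missed infections are also never seen again, the shift is away from 1: with in-trial vivax hazards and an assumed post-trial hazard of 0.005 per day, from 0.564 to 0.542, 0.504 and 0.459 at symptom-free shares of 20%, 50% and 80%.

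**The case against.** The strongest reply is that the protocol has already seen this. It gives the missing LPF as its reason for adding (ii), and Secondary aim 2 and the Sub-study 2 title both ask about symptomatic malaria found passively, which is what (ii) measures. On that view (i) is a companion analysis with a disclosed limitation, and its labelling could sit in an analysis plan that is not shown. The disclosure stands, and nobody should say that the protocol overlooked the problem. But (ii) stands beside (i) and does not replace it. Nothing calls (i) descriptive, and the half-life comparison is fixed for each scenario.

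A reader might infer more: that the treatment HR from (i) is biased and makes protection look longer-lasting. The documents do not support that as a general statement. A Cox model absorbs a fall in detection common to all arms, and the HR moves only under further conditions, in a direction that depends on them. A waning effect is plausible in a study of prophylaxis duration, but its timing is not given. Nor does open-label treatment by itself show that care-seeking or detection differs by arm. If it did differ, the HR would shift (in one vivax illustration, detection of 50% versus 40% moves it from 0.423 to 0.389).

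It is also fair to object that (ii) is not clean. Its detection also changes from active to passive, and children with in-trial LPF have no ACPR, so they fall outside post-trial surveillance. That stands, and the fix must deal with it.

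**Conclusion.** The point holds for rates and mean event-free time. Whenever some infections are symptom-free, analysis (i) understates the post-trial rate by that share and overstates mean event-free time: from about 131 to 143-164 days at an assumed 42-day risk of 20% and 30-70% symptom-free. The size rests on those assumptions and on constant hazards. The direction does not, provided that the mean accounts for children without an event.

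For the treatment HR the point is conditional. There is no change under proportional hazards with equal detection when missed infections leave later risk unchanged. The HR moves away from 1 if the effect wanes after Day 42, and toward 1 if hazards are otherwise proportional but missed infections are never seen again.

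This concerns one of two analyses in a secondary sub-study. The primary endpoints, sample size and safety analyses are untouched. It should be changed because the affected quantity feeds the sub-study's own hypothesis test and the change is cheap.

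**What to change.** In Sub-study 2, Methods:

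- Censor analysis (i) at the last scheduled slide, at most Day 42.
- Use analysis (ii), symptomatic parasitaemia, for the Cox analysis and the half-life comparison that extend into the post-trial months.
- In (ii), estimate treatment effects separately for the in-trial and post-trial periods, because detection changes at Day 42 there too.
- State that children with in-trial LPF are censored in (ii), since post-trial surveillance covers only children with an ACPR.

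This takes a few lines of text and no new data. The cost is that (i) then gives no estimate beyond Day 42, which it could not give validly, and largely overlaps with the 42-day endpoints of the main study. Analysis (ii) becomes the only source for long-term duration, with the limits noted above.

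### Sub-study 2 sets a plain mean time to event against drug half-life although follow-up is censored; the mean needs a stated horizon or should be replaced by a Kaplan-Meier quantile

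*Protocol*

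**What the plan says.** Secondary aim 2 reads "To determine the duration of post-treatment prophylaxis using passive case detection of symptomatic malaria infections", over the six months after trial follow-up. Sub-study 2 takes this up with the hypothesis "The duration of post-treatment prophylaxis for AL, AP and AN is a function of the" elimination half-life of the non-artemisinin partner drug alone.

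The follow-up has two parts:

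- In the trial, "Standardized review including microscopy will be scheduled on Days 1, 2, 3, 7, 14, 28 and 42".
- Afterwards, "We will carry out a 6-month period of passive case detection of all trial patients with an ACPR after trial close-out", using clinic and inpatient records.

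The Sub-study 2 Methods give two analyses. First, "we will perform a Cox regression analysis of time to first appearance of" any parasitaemia and, as a second outcome "because LPF would not be ascertained during post-trial follow-up, any symptomatic parasitaemia in-trial or post-trial". Second, "The mean time to event in each treatment group will be compared with the" half-life, for each of these outcomes. No horizon, restriction or rule for children without an event is attached to that mean.

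**The concern.** The comparison of mean time to event with half-life is the only stated step that connects the data to the half-life hypothesis. Observation ends at a fixed point, so a child with no episode by then contributes only a lower bound on the time to event.

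A plain mean then has two natural readings, and both are poor:

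- An unrestricted mean needs a model for what happens after surveillance stops.
- An average over children who had an event is capped by the length of the window and is too low.

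There is a further difficulty even without censoring. Time to the next episode is the protected period plus the wait for a new infection or relapse after protection has gone. The second part reflects transmission, and it can be much the longer of the two. A mean set beside a half-life may therefore say little about how long the drug protected, which is what secondary aim 2 asks.

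**Working it through.** Sub-study 2 gives no sample size, event rate or power, so there is no figure of the plan to reproduce. The check is how far the possible means differ.

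**Inputs from the protocol**

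- Follow-up: 42 days plus six months (taken as 183 days), so τ = 42 + 183 = 225 days.
- Day 42 figures in the sample-size assumptions: vivax uncorrected response 30.3% for AL and at least double that (60.6%) for the two new combinations; falciparum PCR-corrected response 95.2% for AL.
- Half-lives: lumefantrine 4-6 days, pyronaridine 7-9 days, naphthoquine 2 to 12 days.

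**Check 1: constant hazard (assumed), extended from Day 42**

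- Hazard: r = −ln(S42)/42
- Share censored at τ: S = exp(−rτ)
- Unrestricted mean: 1/r
- Restricted mean: (1 − S)/r
- Events-only mean: (restricted mean − τS)/(1 − S)

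For S42 = 0.606: r = 0.5009/42 = 0.01193 per day; S = exp(−2.683) = 0.068; 1/r = 83.9; restricted mean = 83.9 × 0.932 = 78.1; events-only mean = (78.1 − 15.4)/0.932 = 67.3.

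| Event-free at Day 42 | Censored at 225 d | Unrestricted | Restricted | Events only |
|---|---|---|---|---|
| 30.3% (vivax, AL) | 0.2% | 35.2 | 35.1 | 34.8 |
| 60.6% (vivax, new drugs) | 6.8% | 83.9 | 78.1 | 67.3 |
| 95.2% (low rate, illustration only) | 77% | 854 | 198 | 108 |

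The last row borrows a PCR-corrected recrudescence figure, which is not the sub-study outcome. It only shows what a low event rate does.

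**Check 2: protected period D, then constant incidence (both assumed)**

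With r = incidence/365.25, S = exp(−r(τ − D)), the unrestricted mean is D + 1/r and the restricted mean is D + (1 − S)/r. For D = 28 days:

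| Episodes per child-year | Censored | Unrestricted | Restricted | Events only |
|---|---|---|---|---|
| 0.5 | 76% | 758 | 201 | 122 |
| 1 | 58% | 393 | 180 | 118 |
| 2 | 34% | 211 | 149 | 109 |
| 4 | 12% | 119 | 109 | 94 |

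Protection is the same 28 days in every row, yet the unrestricted mean ranges over 758/119 = 6.4-fold. Lengthening D from 14 to 42 days at fixed incidence moves the unrestricted mean by 28 days, the events-only mean by 16 to 23 days (114 to 130 at the lowest incidence, 82 to 105 at the highest) and the restricted mean by 7 to 25 days (197 to 204; 96 to 121).

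**Check 3: a Kaplan-Meier quantile in the same model**

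Time to 25% with an event is D + ln(4/3)/r. At 4 episodes per child-year, ln(4/3)/r = 0.2877 × 91.3 = 26 days, so D = 14 and 42 give 40 and 68 days and the full 28-day shift is kept. At 0.5 per child-year, 0.2877 × 730.5 = 210 days, so D = 28 gives 238 days, which lies beyond 225 and is not reached.

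**Check 4: the Cox effect under waning protection**

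Take 14 against 42 days of full protection with equal hazard afterwards. Per child in each arm, the shorter-protected arm has e = 1 − exp(−28r) events between Days 14 and 42. With s = exp(−28r) and g = 1 − exp(−183r), later events are sg and g. The large-sample overall hazard ratio θ solves g = eθ/(1 + θ) + (sg + g)θ/(θ + s). This gives 0.85, 0.84, 0.81 and 0.74 at 0.5, 1, 2 and 4 episodes per child-year. The ratio after Day 42 is 1 by construction. The overall value is a valid average but does not show when protection ends.

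**The case against.** The strongest reply has five parts.

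1. **The mean is not the whole analysis.** Cox regression, named first, handles right censoring and gives the between-arm comparison. This stands. A reader might infer that the prophylaxis question cannot be answered or that the Cox model is wrong; the protocol supports neither. One hazard ratio does not locate the end of protection, but effects that vary with time are ordinary content for an analysis plan that is not shown.
2. **The mean may be meant as restricted.** The main study uses Kaplan-Meier and log-rank methods, and an analysis plan could define the mean suitably. This stands against any claim that the mean cannot be estimated: a restricted or parametric mean can be. It does not remove the point that the protocol names a plain mean for data with a fixed end of follow-up.
3. **Averaging only children with events is one reading, not a stated plan.** A reader might infer that large true differences will be hidden. For example, with 40% and 80% having events by Day 224, true means of 438.5 and 139.2 days (3.2-fold) become 102.5 and 83.2 (1.2-fold). Those event rates are assumed, and the restricted means of 175 and 111 days also compress the contrast, to 1.6-fold. The example does not size the problem in this trial.
4. **Censoring may be slight.** On the protocol's vivax figures it is 0.2% to 6.8%. That too is an extrapolation, and detection after Day 42 is passive and symptomatic, which would lower observed rates.
5. **Randomization in blocks by site balances transmission between arms on average.** True of differences between arms; the stated step compares each arm's mean with a half-life, where transmission does enter.

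**Conclusion.** The concern holds in a limited form. As worded, the mean time to event is not identified without extrapolating beyond about Day 225. It is biased downward if only children with events are averaged, and it mixes duration of protection with transmission.

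The size cannot be fixed from the protocol, which gives no event rate for the surveillance period. It is negligible if recurrence is as high as in the earlier vivax AL arm (35.2 against 35.1 days). It is large if recurrence is low (854, 198 or 108 days depending on the definition). These figures rest on constant hazards, a six-month period of 183 days, and assumed incidences and protected periods.

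The comparison with half-life is also weak for a separate reason: three drugs give three half-lives, one quoted over a six-fold range (2 to 12 days), so a dependence on half-life alone cannot be tested in any strong sense. For the any-parasitaemia outcome, detection changes after Day 42; the protocol partly deals with this through its symptomatic outcome.

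This affects a secondary aim only. The primary endpoint is untouched.

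**What to change.** In the Sub-study 2 Methods:

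- Replace the mean time to event with restricted mean event-free time to stated horizons common to all arms, or with a Kaplan-Meier quantile such as the time to 25% with an event. Give each by arm with a confidence interval.
- Say what is reported if the quantile is not reached. The restricted mean still depends on transmission, and a quantile keeps a shift in protection more directly when it can be estimated.
- Describe the comparison with half-life as descriptive only.
- As a supporting analysis, report the Cox treatment effect by period since treatment, with cut-points inside Days 0-42 (for example at the Day 14, 28 and 42 visits) as well as after Day 42. One interval covering Days 0-42 would be too coarse for half-lives of 2 to 12 days.

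No new data are needed. The cost is a change of wording, a little extra analysis, and less precise estimates within each period than for the overall effect.
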